## **9. SAFETY MONITORING AND REPORTING**

### **9.1 Data Monitoring Committee**

An independent Data Monitoring Committee (DMC), consisting of experts in intensive care, clinical research and biostatistics will be established before patient enrolment and will review all trial protocols. The role of the DMC will be to provide study oversight to ensure

that the rights and safety of patients involved in the study are protected by reviewing reported AEs and making recommendations to the Management Committee (MC). Intensive care patients experience a number of common aberrations in laboratory values, signs and symptoms due to the severity of the underlying disease and the impact of standard therapies. Intensive care patients will frequently develop life-threatening organ failure(s) unrelated to study interventions and despite optimal management. Therefore, consistent with established practice in academic ICU trials, events that are part of the natural history of the primary disease process or expected complications of critical illness will not be reported as SAEs in this study. All AEs which are considered to be potentially causally related to the study intervention or are otherwise of concern in the investigator's judgment will be reported.

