#### 4.5 Duration of Study Treatment

Treatment will continue until one of the following criteria for treatment cessation is met:

- 1) For Xuebijing group-5 days of Xuebijing Injection treatment has been administered
- 2) For control group -5 days of placebo has been administered

- 3) Patient is discharged from ICU
- 4) Death occurs
- 5) Serious adverse events suspected to be related to a study medication develops
- 6) Development of a contraindication to any of the study drugs
- 7) Consent has been withdrawn or consent to continue has not been granted

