## 9.2 Adverse event (AE) / Adverse Reaction (AR)

An AE is any untoward medical occurrence in a clinical trial participant administered a medicinal product and does not necessarily have a causal relationship with this treatment. It is recognized that the patient population with critical illness will experience a number of common aberrations in laboratory values, signs and symptoms due to the severity of the underlying illness and the impact of standard therapies. These will not necessarily constitute an AE unless they are considered to be of concern or related to the study or the intervention in the investigator's clinical judgment. In all cases, the condition or disease underlying the symptom, sign or laboratory value should be reported. An adverse reaction is defined as any untoward and unintended response to an investigational medicinal product related to any dose administered. All AEs judged by either the reporting investigator or the sponsor as having a reasonable possibility of a causal relationship to an investigational medicinal product will qualify as adverse reactions. All of the investigational drugs for this trial are approved drugs in China.

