## 9.3 Serious adverse events (SAE) / Serious adverse reactions (SAR)

A SAE or serious adverse reaction is defined as any adverse event/reaction that: Results in death; Is life-threatening; Requires hospitalization or prolongation of current hospitalization; Results in persistent or significant disability or incapacity; Death is an

expected outcome among patients with septic shock, therefore, death will not be considered a SAE. Standard care of patients with septic shock includes a host of complications that fit the definition of an SAE. Medical and scientific judgment will be exercised by the site principal investigator in deciding whether an adverse event/ reaction will be classified as serious in other situations to avoid over reporting.

Specific serious adverse reaction: Suspected or confirmed anaphylactic or anaphylactoid reaction towards one of the study drugs

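### Section 9.3 excludes every death from SAE status without exception, against its own definition and Section 7.1, so a suspected drug-related death can miss the 24-hour report and the SAE outcome

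*Protocol*

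**What the plan says.** **Definition.** Section 9.3 opens with "A SAE or serious adverse reaction is defined as any adverse event/reaction that: Results in death; Is life-threatening", and goes on to hospitalization and disability. It also names suspected or confirmed anaphylaxis to a study drug as a specific serious adverse reaction.

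**Death.** The same section then says that death is an "expected outcome among patients with septic shock, therefore, death will not be considered a SAE". Section 7.1, on data collection, instead groups deaths together with the other SAEs.

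**ICU complications.** Section 9.1 gives as background that "Intensive care patients will frequently develop life-threatening organ failure(s) unrelated to study interventions and despite optimal management". From this it concludes that natural-history events and "expected complications of critical illness will not be reported as SAEs in this study". The next sentence adds that "All AEs which are considered to be potentially causally related to the study intervention", or that otherwise concern the investigator, will be reported.

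**Relatedness elsewhere.** Section 9.2 says of common ICU abnormalities: "These will not necessarily constitute an AE unless they are considered to be of concern or related to the study or the intervention". It classes as adverse reactions the AEs judged by the investigator or the sponsor as "having a reasonable possibility of a causal relationship to an investigational medicinal product will qualify as adverse reactions". Section 4.5, item 5, lists as a reason to stop treatment: "Serious adverse events suspected to be related to a study medication develops".

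**Where the label matters.** Section 9.4 sets a 24-hour limit for reporting SAEs to the coordinating centre. It sets no limit for AEs, and the deadline sentence does not name SARs. Section 5.3 lists two safety outcomes, SAE incidence and AE incidence.

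**The concern.** The death sentence removes a whole class of events from SAE status by outcome, whatever the suspected cause. A death that the investigator attributes to the infusion meets the seriousness definition and the exclusion at once, and the protocol does not say which prevails. A site that follows the exclusion has no 24-hour duty for that death and does not count it in the SAE outcome.

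The 9.1 exclusion raises a weaker form of the same question. Some drug reactions could look like complications of sepsis. As an illustration only, the Introduction describes the product as acting on coagulation and platelets, and it describes sepsis itself as disturbing coagulation. Section 9.1 has such an event reported if it is thought related, but does not say under which label or how fast.

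At stake are the speed of expedited reporting and the completeness and consistency of one safety outcome across up to 45 centres.

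**Working it through.** The plan gives no figure on this point to reproduce, so the check is to set the sections side by side and follow two events through them.

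**Event A: a death suspected to be caused by the study drug.**

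1. Section 9.2: a reasonable possibility of causality makes it an adverse reaction.
2. Section 9.3, definition: a reaction ending in death is an SAE or serious adverse reaction.
3. Section 9.3, death sentence: it is not an SAE. No relatedness condition is attached. The reason given concerns septic shock, while Section 3.3 enrols sepsis with a SOFA score of 2 to 13, so the reason does not describe every enrolled patient.
4. Section 7.1: deaths are treated as SAEs.
5. Steps 2 and 4 say yes and step 3 says no, with no order of precedence. If step 3 prevails, the event may survive as an SAR. But the 9.4 deadline sentence names only SAEs, and 5.3 counts only SAEs and AEs. The event then has no stated deadline and no place in SAE incidence.

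**Event B: a non-fatal, life-threatening event that resembles an ICU complication and is suspected to be drug-related.**

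1. Section 9.1, exclusion: an expected complication is not reported as an SAE. The sentence itself carries no relatedness condition.
2. Section 9.1, preceding sentence: the rationale is organ failure unrelated to the intervention, which suggests that only unrelated events were meant.
3. Section 9.1, following sentence: potentially related AEs are reported. Class and timing are not given.
4. Sections 9.2, 9.3 (definition) and 4.5, item 5, all point to treating it as serious.
5. Event B is therefore reported. What stays open is whether it goes in as an SAE within 24 hours.

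Section 9.2 shows how the gap could have been closed: for AE status it writes the exception out. Neither 9.1 nor the 9.3 death sentence has matching words for SAE status.

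**What depends on the label.**

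| Item | Depends on SAE status? |
|---|---|
| 24-hour report (9.4) | Yes |
| SAE incidence (5.3) | Yes |
| AE incidence (5.3) | No |
| DMC review of reported AEs (9.1) | No |
| Primary outcome, 28-day mortality (5.1) | No |

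So 1 of the 2 safety outcomes is touched.

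**Reach of the death rule, for scale only.** Section 8.1 assumes 24.3% mortality on placebo and an absolute reduction of 6 points, hence 24.3% − 6% = 18.3% on treatment, with 1800 patients, or 900 per arm.

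- All randomized patients: 900 × 0.243 + 900 × 0.183 = 218.7 + 164.7 = 383.4, about 383 deaths.
- After the planned 15% dropout: 1800 × 0.85 = 1530, or 765 per arm; 765 × 0.243 + 765 × 0.183 = 185.9 + 140.0 = 325.9, about 326 deaths.

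The death sentence thus covers roughly 326 to 383 expected deaths. The number misrouted would be that total times the fraction suspected to be drug-related. The protocol gives no such fraction, so the product cannot be computed. The range is not an estimate of lost reports.

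**The case against.** The strongest reply is that the sections, read together, already treat a related serious event as serious. The 9.1 exclusion speaks of natural history and of complications of the illness, which are statements about cause. An event blamed on the drug is arguably outside both. The rule follows from a sentence about unrelated organ failure, and the next sentence brings related AEs back. The stopping rule in 4.5 would have little to act on if related SAEs lost their label. Excluding expected ICU events is also an openly stated choice that the protocol describes as usual in academic ICU trials.

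For 9.1 most of this stands. A reader might infer that 9.1 lets suspected drug reactions go unreported; the text does not support that. Only class and deadline are unsettled.

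For 9.3 the reply is weaker. One can read the death sentence as excluding death as an outcome while the reaction that led to it stays serious. That is a reasonable reading, but the section does not state it, and sites could differ. Fatal anaphylaxis is protected by being named as a serious reaction; other fatal reactions have no such wording. It is also fair to say that deaths are fully captured by the primary outcome and by data collection. That secures the count of deaths, but gives no expedited report of a suspected cause.

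Section 9.4 mentions a separate case report form, which is not shown and may tell sites how to classify these events.

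**Conclusion.** The point holds for the death sentence in 9.3: it is unconditional, and it conflicts with the definition in its own section and with 7.1. For 9.1 it holds only as an ambiguity about class and timing, and the intent was probably to exclude unrelated events alone.

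Severity is minor. The effect is confined to the 24-hour report and to one of two safety outcomes. A suspected-related event is still an AE that must be reported and can reach the DMC.

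Two stronger conclusions are tempting and should not be drawn. One is that the SAE comparison is biased toward one arm: Section 4.4 keeps investigators and evaluators blinded, and nothing in the document shows that classification would differ by arm. The other is that the mortality result is at risk: the primary outcome counts every death whatever its SAE status.

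The verdict rests on sites following Section 9 as written, and on no unseen site instruction settling the conflict. This is not a matter for the analysis plan, because SAE definitions and deadlines are site instructions and a later plan cannot recover a missed 24-hour report.

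**What to change.** Add one clause to the death sentence in 9.3 and, for consistency, to the exclusion in 9.1: *unless the investigator or the sponsor considers that the study drug may reasonably have caused the event (the test in 9.2), in which case it is reported within 24 hours and counted as an SAE*.

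In 9.4, name SARs beside SAEs in the 24-hour rule. The clause would work without this, since it states the deadline itself, but naming SARs makes the deadline match the joint definition in 9.3.

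Leave the exclusion of unrelated expected events as it is, so that over-reporting stays controlled.

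The cost is a short wording change in three places and a memo to sites. The downside is a few more expedited reports, limited to events suspected to be drug-related. Sample size and primary analysis do not change.

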## 9.2 Adverse event (AE) / Adverse Reaction (AR)

An AE is any untoward medical occurrence in a clinical trial participant administered a medicinal product and does not necessarily have a causal relationship with this treatment. It is recognized that the patient population with critical illness will experience a number of common aberrations in laboratory values, signs and symptoms due to the severity of the underlying illness and the impact of standard therapies. These will not necessarily constitute an AE unless they are considered to be of concern or related to the study or the intervention in the investigator's clinical judgment. In all cases, the condition or disease underlying the symptom, sign or laboratory value should be reported. An adverse reaction is defined as any untoward and unintended response to an investigational medicinal product related to any dose administered. All AEs judged by either the reporting investigator or the sponsor as having a reasonable possibility of a causal relationship to an investigational medicinal product will qualify as adverse reactions. All of the investigational drugs for this trial are approved drugs in China.

## 9.3 Serious adverse events (SAE) / Serious adverse reactions (SAR)

A SAE or serious adverse reaction is defined as any adverse event/reaction that: Results in death; Is life-threatening; Requires hospitalization or prolongation of current hospitalization; Results in persistent or significant disability or incapacity; Death is an

expected outcome among patients with septic shock, therefore, death will not be considered a SAE. Standard care of patients with septic shock includes a host of complications that fit the definition of an SAE. Medical and scientific judgment will be exercised by the site principal investigator in deciding whether an adverse event/ reaction will be classified as serious in other situations to avoid over reporting.

Specific serious adverse reaction: Suspected or confirmed anaphylactic or anaphylactoid reaction towards one of the study drugs

#### 9.4 Reporting AEs/ARs and SAEs/SARs

Adverse events/reactions and serious adverse events/reactions will be recorded on a separate case report form. SAEs should be reported to the coordinating centre within 24 hours of study staff becoming aware of the event. The coordinating centre staff will be responsible for following-up all events to ensure all details are available.

The coordinating centre is also responsible for reporting directly to HRECs and investigators, who forward any relevant information to their institution. Copies of any reporting and correspondence to and from the local HREC should also be sent to the coordinating centre.

#### 9.6 Post-Trial Care

If post-trial care for compensation to those who suffer harm from trial participation will be covered by Ping An Clinical Trial Liability Insurance.

### 10. FUNDING

This study is funded by the Development Center for Medical Science and Technology, National Health Commission of the People's Republic of China (WK-2016-HR-03).

None of the funding organizations will contribute to the study design; collection, management, analysis and interpretation of data; writing of the report or the decision to submit the report for publication.

## Protocol Amendments

**SUBJECT:** Summary of Changes to Protocol 1.1: *Efficacy of Xuebijing Injection in Patients with Sepsis: A Multicentre, Randomized, Blind, Placebo-controlled Trial (EXIT-SEP TRIAL)*

This is a summary of Protocol Changes (1 amendment) during the study. The changes were made under the applicable section of the protocol was updated accordingly.

| Change in Section(s) & Page Number(s) | Initial wording in Protocol Version 1.0                                                                                                                                                                                                                                                                                                   | Amended or New wording in Protocol Version 1.1                                                                                                                                                                                                                                                                                                                                                                                             |
|---------------------------------------|-------------------------------------------------------------------------------------------------------------------------------------------------------------------------------------------------------------------------------------------------------------------------------------------------------------------------------------------|--------------------------------------------------------------------------------------------------------------------------------------------------------------------------------------------------------------------------------------------------------------------------------------------------------------------------------------------------------------------------------------------------------------------------------------------|
| Outcomes section, page 3 # | Secondary outcomes will be the improvement of SOFA scores, the improvement of the Acute Physiology and Chronic Health Evaluation II score (the improvement means the difference of score between the day enrolled in the study and the 6 days), duration of mechanical ventilation, mortality in the ICU and duration of stay in the ICU. | Secondary outcome
1) In ICU mortality
2) In hospital mortality
3) Length of stay (LOS) in the ICU
4) LOS in hospital, 28-day cumulative mechanical ventilation-free days
5) 28-day ICU-free days
6) The change in SOFA score on day 3
7) The change in SOFA score on day 6
8) The change in Acute Physiology and Chronic Health Evaluation (APACHE) II score on day 3
9) The change in APACHE II score on day 6 |

